#### Criteria for discontinuing or modifying allocated interventions {11b}

Participants can discontinue (a) allocated trial treatment or (b) providing data to the trial, at any time. In both cases all efforts ethically appropriate will be made to report the reason for discontinuation as thoroughly as possible on the withdrawal form.

Should a participant wish to discontinue allocated trial treatment, efforts will be made to continue to obtain follow-up data, with the permission of the patient or family/ friend/ carer, as appropriate. They may also be invited to take part in a qualitative interview, as part of the investigation of acceptability of the trial treatment arms/processes. On discontinuation of allocated treatment, the participant will return to usual care as deemed appropriate by their treating clinical team.

#### Strategies to improve adherence to interventions {11c}

Process information is documented in the electronic Clinical Team Activity Record (CTAR). The CTAR is updated every time there is contact with a patient or carer or HCP. The research nurse uses the CTAR alongside the clinical notes to capture delivery of relevant components of care to patients in both arms of the trial in the follow-up case report form (CRF). Compliance is also monitored through regular site compliance surveys. Identified compliance issues are addressed with sites and additional training provided, as required.

The primary analysis is intention-to-treat. For this reason, even if a patient is documented as deviating from protocol or withdrawing from their randomised treatment, they will be encouraged to continue with study visits/contacts and patient questionnaires.

#### Relevant concomitant care permitted or prohibited during the trial {11d}

Participants in both arms can receive any routine NHS care considered appropriate by their treating clinical team, with the following exceptions:Participants randomised to prepare for responsive management will be considered to have discontinued allocated treatment if they make a decision, recorded in their medical records, with their clinical team to make plans to prepare for renal dialysis, or have a dialysis access procedure (surgery or line insertion) for kidney failure, or start dialysis for kidney failure.Participants randomised to prepare for renal dialysis will be considered to have discontinued their allocated treatment if they make a decision, with their clinical team, recorded in their medical records and in a letter to the GP, not to start dialysis in the future, even if they become symptomatic of kidney failure.

#### Provisions for post-trial care {30}

Following the end of the trial, continued provision of conservative kidney management in the format specified for the trial (i.e. responsive management) will be at the discretion of the treating clinical team and is likely to depend on the trial results. Participants will be informed of this in the written information given to them when they are considering entering the trial.

#### Outcomes {12}

##### Primary outcome measure

The primary outcome is the mean total number of QALYs observed in the two arms between first patient recruited and the end of data collection (31st August 2025), using the EQ-5D-5L measured 4 monthly during this period to derive the health utility value with appropriate imputation methods for missing values and the area under the curve approach. After death, patients are allocated a utility value of 0 therefore continue to contribute data to the study regardless of survival. Based on projected recruitment patterns, we estimate we will have, on average, 3 years of data on patients from which to calculate QALYs (i.e. on average at least 3 years of data from first patient recruited to end of data collection).

This outcome has been chosen after extensive discussion with patients and patient groups who were very clear that they care about both quality of life and quantity of life, and evidence that patients may be willing to forgo some quantity of life for better quality of life [24].

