#### Sample size {14}

A sample size of 512 has 90% power to detect a difference between the pathways of 0.345 QALYs (5% two-sided) over 3 years of follow-up based on EQ-5D-5L. A discrete choice experiment in 8 kidney units in Australia suggests that patients with kidney failure are willing to forgo 7 months of life expectancy to reduce the number of visits to hospital for dialysis by one per week [24]. Responsive management reduces visits to hospital. Based on a median EQ-5D utility value for being alive on dialysis of 0.69 [34], 7 months of life at this value would equate to 0.4 QALYs. We wanted to be able to detect a slightly smaller difference than this of 6 months between the two pathways, equivalent to 0.345 QALYs.

For the purposes of informing our calculation, we examined data from a longitudinal study [35] of patients with CKD where utility score data were available at multiple points during follow-up. In that particular study, patients were followed up from eGFR 20–30 ml/min/1.73 m^2^ until start of dialysis or end of follow-up. From these data, we calculated total QALYs over 3 years of follow-up (based on EQ-5D).

The data suggested a bimodal distribution (means 0.36 and 2.4). While we cannot exclude the possibility that a larger sample would have yielded a unimodal distribution, bi-modal distributions of EQ-5D values (which are used to calculate QALYs) have been noted in a variety of conditions including rheumatoid arthritis [36, 37] and cancer [38]. Explanations for such distributions include the algorithm used to calculate the EQ-5D score itself which tends to cluster scores in the extremity close to 1.0 (perfect health) and near 0.45 (representing moderate health) [39].

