#### Primary outcome analysis

The primary endpoint in this study is quality-adjusted life years which will be calculated using EQ-5D-5L data collected 4-monthly and survival data. The primary statistical analyses between the randomised groups will be conducted on a modified intention-to-treat basis including all participants contributing at least one quality of life measurement. Utility scores will be estimated from the EQ-5D-5L using the NICE-recommended approach at the time of analysis and these will be used to compute QALYs experienced over the follow-up period using the area under the curve approach. Depending on the distribution of the observed QALYs data, appropriate regression techniques will be applied. If normally distributed, the mean differences in QALYs between treatment arms with 95% confidence intervals will be calculated using multivariate linear regression models. Otherwise, the shape of the distribution will be considered to inform the choice of alternative, suitable regression models (including non-parametric models) for this outcome. All models will adjust for baseline EQ-5D-5L scores.

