## Trial status

Recruitment commenced in July 2017 and is scheduled to complete by end of August 2024. Follow-up is expected to continue to end of August 2025. The current protocol is version 10.0, dated 26 June 2024.

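### The primary outcome totals QALYs to one calendar date, with 1 to about 8.2 years of potential follow-up, but its target difference and power are for QALYs over exactly 3 years

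*Protocol article*

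**What the plan says.** Outcomes {12} defines the primary outcome as the "mean total number of QALYs observed in the two arms between first patient recruited and the end of data collection (31st August 2025"), with death scored as utility 0. It adds: "we estimate we will have, on average, 3 years of data on patients from which to calculate QALYs". A gloss in the same sentence calls this an average of at least 3 years.

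Trial status gives the calendar: "Recruitment commenced in July 2017 and is scheduled to complete by end of August 2024", and "Follow-up is expected to continue to end of August 2025".

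Sample size {14} works on a different horizon. It claims "90% power to detect a difference between the pathways of 0.345 QALYs (5% two-sided) over 3 years of follow-up". The planning data are on the same footing ("we calculated total QALYs over 3 years of follow-up (based on EQ-5D"), and simulated values above 3 were thrown away. The later reduction from 512 to 446 participants, for 85% power, reuses those simulations and assumptions.

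The Primary outcome analysis section computes QALYs over the follow-up period and leaves the type of regression to the observed distribution. It names one adjustment: "All models will adjust for baseline EQ-5D-5L scores". For hospital-free days, the Secondary outcome analysis section mentions a negative binomial model with an offset for follow-up time as a candidate. No corresponding term is named for QALYs. Detail is deferred to an analysis plan that is not shown.

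**The concern.** Someone randomised at the end of August 2024 can accrue at most 1 QALY by the cut-off; someone randomised in July 2017 could accrue about 8. The target and power describe an outcome that cannot exceed 3 for anyone.

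Two things follow. First, the between-arm difference becomes an average over the accrual pattern. The same treatment effect would give a different number had sites recruited faster or slower, so 0.345 (six months of life at utility 0.69) has no single meaning on this scale. Second, variation in follow-up length adds variation to the outcome that has nothing to do with treatment. Unless the model removes it, it widens the confidence interval. Both bear on the trial's main result.

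**Working it through.** **1. Range of follow-up (dates from Trial status and Outcomes {12}).** 1 July 2017 to 31 August 2025 is 8.17 years (8.08 if the first participant joined at the end of July). 31 August 2024 to 31 August 2025 is 1.0 year. Even accrual over 8.17 − 1.0 = 7.17 years would average (1 + 8.17)/2 ≈ 4.6 years, with 2/7.17 = 28% under 3 years. An average of 3 therefore needs accrual weighted towards the later years. With an assumed shape of 1 + 7.17 × Beta(1, 2.585), whose mean is 1 + 7.17/3.585 = 3.0, 57% of participants have less than 3 years.

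**2. The plan's own figures.**
- Target: 0.69 × 0.5 year = 0.345.
- Loss to follow-up: 2 × 230 = 460, and 460/0.90 = 511.1, taken up to the even total of 512.
- 85% power: 512 × [(1.960 + 1.036)/(1.960 + 1.282)]² ≈ 437, within 3% of the stated 446. Evaluable per arm: 446 × 0.9/2 ≈ 200.
- The 90% power at 230 per group could not be confirmed. The arguments of the simulation command are unlabelled, and plausible readings gave power from 58% to about 100%. This does not show that 230 is wrong.

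**3. What one constant benefit is worth at different horizons.** Assumptions: exponential survival with 3-year survival S of 40% or 55% (the registry figures in the Background) and utility 0.69 (Sample size {14}). The hazard is h = −ln(S)/3, and mean QALYs over F years are 0.69 × (1 − e^(−hF))/h.

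For a utility benefit d, the difference is d × (1 − e^(−hF))/h. With S = 40%, h = 0.305 and 3-year mean survival time is 0.6/0.305 = 1.96 years, so d = 0.345/1.96 = 0.176. At F = 1 the difference is 0.176 × 0.862 = 0.15; at F = 8.17 it is 0.176 × 3.00 = 0.53. The survival benefit uses a constant hazard ratio chosen to give 0.345 at 3 years (0.44 for S = 40%, 0.29 for S = 55%).

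| Benefit, scaled to 0.345 at 3 years | 1 year | 8.17 years | Averaged, mean follow-up 3 | Averaged, even accrual (mean 4.6) |
|---|---|---|---|---|
| Utility | 0.14–0.15 | 0.53–0.62 | 0.32–0.33 | 0.40–0.43 |
| Survival | about 0.05 | 1.3–1.7 | 0.37–0.39 | 0.66–0.77 |

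**4. Spread of the outcome.** With the same survival and an assumed between-person utility SD of 0.2, the SD of total QALYs is:
- 0.83–0.85 at a fixed 3 years;
- 0.98–1.07 with follow-up averaging 3 years (0.90–0.93 after removing follow-up length);
- 1.34–1.51 with even accrual (1.28–1.38 after removing it).

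For comparison, 230 per group at 90% power would imply, for a t-test, an SD of 1.14 at a difference of 0.345, or 1.03 at 0.345 × 0.90 = 0.31. The factor 0.90 reflects the plan's 5% crossover in each arm.

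**5. Power with and without potential follow-up in the model.** Simulated with 200 per arm, a 3-year effect of 0.31 allowed to vary with follow-up as in step 3, and linear regression already adjusting for baseline EQ-5D-5L. With mean follow-up of 3 years:
- utility benefit: 75–79% without the covariate, 85–87% with it;
- survival benefit: about 90% without, 96–99% with.

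Across eight scenarios (two survival levels, two accrual shapes, two kinds of benefit) the covariate never lowered power.

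**The case against.** Total QALYs to a common close is a legitimate comparison. Follow-up length is fixed by randomisation date, so it is balanced between arms in expectation and a bias claim would fail. The outcome also counts survival beyond 3 years, which fits the protocol's reason for choosing it: patients care about quantity as well as quality of life. All of this stands.

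A reader might infer that the primary model ignores follow-up length. The article does not establish that. It names one covariate without closing the list, leaves the model open and defers to an analysis plan. The suggestion to add the covariate is therefore an improvement available at no cost, not a charge of missing detail.

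A reader might also infer that the trial is underpowered. The documents do not show it. At the plan's own average of 3 years, the illustrative SD (0.98–1.07) lies near or below the 1.03–1.14 that the planned size would imply for a t-test, and the averaged effect (0.32–0.39) stays close to 0.345. The larger distortions come from even accrual, which averages 4.6 years and is not what the protocol projects.

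Finally, a reader might want QALYs restricted to 3 years as the primary outcome. That is a debatable trade. If follow-up averages 3 years, more than half of participants have less than 3 years available, so most would need weighting or imputation, and later survival would be set aside. Changing the primary outcome this late in an unblinded trial would also be a substantial step.

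What the objection leaves untouched is the mismatch between endpoint and target. Both are protocol content, and they conflict within this document.

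**Conclusion.** The point holds as one of precision and interpretation. The primary outcome allows 1.0 to about 8.2 years of potential follow-up; the 0.345 target and the 90% and 85% power belong to a 3-year QALY capped at 3. The range of follow-up is date arithmetic and needs no assumption.

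The consequences rest on assumed exponential survival, a mean utility of 0.69 with SD 0.2, and an assumed accrual shape. On those terms the apparent effect moves little if follow-up really averages 3 years, but could reach 0.66–0.77 under even accrual with a survival benefit. Modelling potential follow-up gains roughly 6 to 10 points of power at a mean of 3 years. Whether actual power falls below 85% cannot be settled from the article, because the planning distribution cannot be reproduced and the actual accrual pattern is not given.

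**What to change.** 1. Keep total QALYs to 31 August 2025 as the primary outcome. Add potential follow-up (randomisation date to 31 August 2025) to the primary model alongside baseline EQ-5D-5L. Use potential follow-up, which is fixed at randomisation, and not observed time to death or withdrawal, which treatment can affect.
2. Restate the target difference and power for that endpoint under the actual accrual pattern, or say plainly that 0.345 and the 85% refer to 3-year QALYs.
3. Report QALYs restricted to 3 years from randomisation as a supporting analysis, with administrative censoring handled for those randomised after 31 August 2022, so that the result can be read against 0.345.

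The covariate needs no new data, because randomisation dates are already held. The change should be fixed in writing before any comparison by arm on the primary outcome. The cost is a little more analysis work and possibly a less favourable stated power. The covariate sharpens the estimate but does not remove its dependence on accrual, which is why items 2 and 3 are also needed.

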##### Secondary outcome measures

Survival outcomes (from baseline to the end of follow-up):All-cause mortalityCause-specific mortalityPlace of deathHospital-free days

Patient-reported outcomes:Generic quality of life using the EuroQol 5-dimension 5-level (EQ-5D-5L) [25]Disease-specific symptom burden using the integrated palliative outcome scale-renal (IPOS-renal) [26]Capability gain specific to older persons using the ICEpop CAPability (ICECAP-O) [27]Capability during end-of-life care using the ICECAP-SCM [28]Treatment burden using the multimorbidity treatment burden questionnaire (MTBQ) [29]

Physical functioning outcomes:Timed get up and go [30]—summary score at 12 monthly time points and changes over timeGrip strength (Jamar hand dynamometer) [31]—summary score at 12 monthly time points and changes over time

Relative/carer-reported outcomes:Impact on carers using the PAlliative Care in chronic Kidney diSease impact on carers questionnaire (PACKS) [32]QUALYCARE post-bereavement survey obtaining retrospective information covering the 1 week preceding death, if the patient dies [33].

Health economic outcomes:Incremental cost-per QALY gained from a health and social care provider perspective and a secondary societal perspective including patients and close personsCost per year of full/sufficient capability equivalence gained, from a health and social care provider perspective and secondary societal perspective including patients and close persons.

Patient, relative and HCP-reported acceptability of the treatment arms (particularly, the intervention):Captured through qualitative interviews (see additional file 2).

#### Participant timeline {13}

The time schedule of enrolment, interventions and assessments are shown in a schematic diagram (Fig. 2).

**Fig. 2 Fig2:**
[figure not shown]
Schedule of enrolment, interventions and assessments *Repeated until the end of the follow up period (31 August 2025)

#### Sample size {14}

A sample size of 512 has 90% power to detect a difference between the pathways of 0.345 QALYs (5% two-sided) over 3 years of follow-up based on EQ-5D-5L. A discrete choice experiment in 8 kidney units in Australia suggests that patients with kidney failure are willing to forgo 7 months of life expectancy to reduce the number of visits to hospital for dialysis by one per week [24]. Responsive management reduces visits to hospital. Based on a median EQ-5D utility value for being alive on dialysis of 0.69 [34], 7 months of life at this value would equate to 0.4 QALYs. We wanted to be able to detect a slightly smaller difference than this of 6 months between the two pathways, equivalent to 0.345 QALYs.

For the purposes of informing our calculation, we examined data from a longitudinal study [35] of patients with CKD where utility score data were available at multiple points during follow-up. In that particular study, patients were followed up from eGFR 20–30 ml/min/1.73 m^2^ until start of dialysis or end of follow-up. From these data, we calculated total QALYs over 3 years of follow-up (based on EQ-5D).

The data suggested a bimodal distribution (means 0.36 and 2.4). While we cannot exclude the possibility that a larger sample would have yielded a unimodal distribution, bi-modal distributions of EQ-5D values (which are used to calculate QALYs) have been noted in a variety of conditions including rheumatoid arthritis [36, 37] and cancer [38]. Explanations for such distributions include the algorithm used to calculate the EQ-5D score itself which tends to cluster scores in the extremity close to 1.0 (perfect health) and near 0.45 (representing moderate health) [39].

Based on summary statistics from the observed data and visual inspection of the histogram, we simulated datasets of 1,000,000 observations for comparator groups using the SKBIM command in STATA [40]. This command allows the user to simulate a bimodal distribution while specifying different characteristics of the distribution including means, standard deviations, skewness and kurtosis (for the comparator group the simulated dataset was generated with this command: skbim (0.5 0.359 0.096 2.413 2.413 0.154 1 1000000 123 0.804 2.492 0 3)). To simulate the distribution of QALYs in the intervention group, we assumed the same distribution as the comparator group, but shifted the two means by 0.345 QALYs to reflect a clinically meaningful difference we wanted to be able to detect. Simulated values greater than 3 were discarded.

Sample size calculations involved re-sampling (1000 iterations) with varying sample sizes from these simulated distributions of continuous QALY scores and performing Mann Whitney tests. To allow for possible cross over, we selected our intervention group samples by taking 95% of our sample from the intervention distribution and 5% from the comparator distribution. The same process was used to identify the comparator group sample.

Having 230 patients per group allows detection of a difference between the pathways of 0.345 QALYs with 90% power (2-sided a = 0.05). Death is not a censoring event (utility becomes and remains 0) so loss-to-follow-up should not exceed 10%. Allowing for loss-to-follow-up increased the total sample size to 512.

Following the COVID-19 pandemic, recruitment rates have improved but are still generally tracking below predicted. Following discussions with the Trial Steering Committee (TSC), Patient Advisory Group (PAG) and funder, the Trial Management Group (TMG) has agreed to extend recruitment to ensure 85% power is achieved. Using the original sample size simulations and associated assumptions, this reduces the target sample size from 512 to 446 participants.

#### Recruitment {15}

Patients referred with advanced CKD and receiving education regarding potential treatment options are identified at time of receipt of referral letter, during patients’ clinical appointments, at low-clearance or pre-dialysis clinics, or by searching kidney clinic records. Eligible patients are provided with a study invitation letter and participant information sheet. Patients ineligible due to an eGFR greater than 15 mL/min/1.73 m^2^ can be given a pre-eligibility patient information sheet as part of their kidney education package to introduce the concept of study participation as a future option.

##### Application of the QRI to optimise recruitment

Previous studies in this area have highlighted the need for RCT evidence, but also documented doubts about the viability of such a trial due to anticipated recruitment challenges [6]. In light of these concerns and previous under-recruiting trials in this field [41], we incorporated the QRI to support recruitment to Prepare for Kidney Care. The QRI is a complex intervention, designed to run concurrent to an RCT’s recruitment period, with the aim of identifying and addressing factors that compromise recruitment and informed consent [20]. The QRI’s methods were conceived during the NIHR-funded ProtecT study [42] and refined through application to over 50 other RCTs, following evidence of its success at diagnosing and addressing recruitment issues in challenging trials [20, 43, 44]. The methods underpinning the QRI have been protocolised and are reported elsewhere [20]. In brief, the QRI proceeds via two cyclical phases: phase 1 seeks to rapidly unearth factors that shape recruitment success to the particular RCT by triangulating data from a range of sources: (i) analysis of screening log information, capturing data on numbers of patients screened, eligible, approached and randomised (‘SEAR’) and reasons why patients do not proceed through these stages [45]; (ii) audio-recordings of recruitment discussions where the trial is presented to potential participants and their families/carers; (iii) interviews with trial/site staff and patients and (iv) analysis of trial documentation [46]. Phase 2 draws on these findings to design and deliver tailored ‘actions’ to improve recruitment as the trial is underway. Prepare for Kidney Care is the first renal trial to employ the QRI. Further details of application of QRI methods to Prepare for Kidney Care are available in additional file 3.

